## Abstract

**Background/Objectives**: Approximately 30% of women experience pelvic pain one year after vaginal delivery, and this increases to 50% during vaginal intercourse. Multimodal physiotherapy is the first-line treatment for myofascial pain of the pelvic floor muscles (PFM), often incorporating emerging technologies like radiofrequency, despite limited evidence supporting its use. The RASDOP study aims to (i) evaluate the effectiveness of multimodal physiotherapy combining therapeutic education, PFM training, and myofascial pain syndrome (MPS) management with or without radiofrequency, in reducing pain and improving sexual function postpartum; and (ii) explore the barriers and facilitators influencing adherence and perceived self-efficacy towards physiotherapy treatment in women with postpartum pelvic pain. **Methods**: This study employs a randomized clinical trial with a blinded examiner and two parallel groups, followed by a qualitative phenomenological study. A total of 124 postpartum women with pelvic pain (≥4 cm on the visual analogue scale) will be randomized into two groups: a multimodal physiotherapy group (therapeutic education, MPS treatment, and PFM training) and a radiofrequency + multimodal physiotherapy group (same treatment with additional non-ablative radiofrequency). Both groups will receive 12 supervised individual sessions. Assessments will be conducted pre- and post-intervention, and at 3-, 6-, and 12-month stages post-treatment. Primary outcomes include pain intensity and sexual function, while secondary outcomes involve PFM tone, strength, MPS presence, levator ani length, and distress caused by pelvic floor dysfunction. The qualitative study will utilize semi-structured interviews and focus groups analyzed thematically. **Results**: Radiofrequency is expected to enhance pain relief, sexual function, and PFM relaxation. Insights into adherence and barriers will aid in personalizing physiotherapy interventions. **Conclusions**: The RASDOP study will provide evidence on the safety and efficacy of radiofrequency in postpartum pelvic pain treatment and shed light on women’s experiences to improve therapeutic outcomes.

## 1. Introduction

International scientific and professional societies describe pelvic pain as a significant health concern, particularly when it persists over time [1,2,3], and it is associated with impaired sexual function [4]. Both sexes can experience pelvic pain-related sexual dysfunction, though its prevalence appears to be higher in women. The prevalence of non-cyclic chronic pelvic pain in women is estimated to reach up to 30% [5], while approximately 40–50% of women, regardless of age, have experienced sexual problems at least once in their lifetime [6]. The association between pelvic pain, urogenital pain, and vulvovaginal pain in the female population is strongly linked to alterations in sexual activity, leading to the use of terms that relate pain to sexual dysfunction, such as vaginismus and dyspareunia [2,3,7]. However, this pain can also manifest during other daily activities, be accompanied by other pelvic floor dysfunctions [8], or affect different phases of the sexual response cycle, such as desire, arousal, or orgasm [9].

The etiology and risk factors associated with pain localized to the pelvic areas are multifactorial [10,11]. Pregnancy and vaginal delivery, whether spontaneous or instrumental, have been identified as predisposing and perpetuating risk factors of pelvic and genital pain [12]. This positive association between pregnancy, childbirth, and pelvic and genital pain is observed in up to 34% of women one year postpartum, increasing to 33–52% when pain is triggered during vaginal intercourse, a condition referred to as dyspareunia [12,13]. Furthermore, when considering other domains involved in sexual function, such as arousal, desire, lubrication, or orgasm, a cross-sectional study conducted in 325 women reported that over 60% experienced sexual dysfunction during the first year postpartum, and 70% reported sexual dissatisfaction [14]. The hormonal and biomechanical adaptations of the pelvis to accommodate the baby during pregnancy, the overstretching of the pelvic floor muscles (PFM) and their neural structures during childbirth [15], as well as the lacerations or trauma that may occur in the perineum during the expulsive phase [16,17], appear to be significant sources of pain. Additionally, increased tenderness of the PFM has been observed in women with chronic pelvic pain compared to those without pain, and this has also been associated with dyspareunia [18]. The presence of myofascial pain syndrome (MPS) in the PFM and other muscles related to the abdominopelvic cavity may result in pain and sexual dysfunction, as well as being associated with other symptoms affecting the urogenital and gastrointestinal systems, such as difficulty emptying the bladder, a sensation of vaginal heaviness, or pain during defecation, among others [19].

When addressing pelvic pain, especially associated with tenderness, high tone or the presence of MPS in PFM, multimodal physiotherapy is the first line treatment [2,20]. The multimodal physiotherapy includes different strategies such as PFM training (PFMT), biofeedback, dilators, electrical stimulation, manual therapy or education [21]. Specific PFMT has been shown to be effective in reducing pain in women with provoked vestibulodynia [22] and vaginismus [23], improvements that appear to increase when combined with local manual therapy, resulting in a reduction in pain intensity and an improvement in sexual function [24]. Patient therapeutic education for pain has been proven to be an effective tool that provides self-management strategies for patients [23,25,26] addressing misconceptions, beliefs, and cognitive and behavioral aspects that can modify pain intensity, even preventing its perpetuation or worsening. Furthermore, in clinical practice, non-ablative radiofrequency is increasingly being incorporated into the management of pelvic pain. This tool has made a significant impact in the field of multimodal physiotherapy, and it seems to induce local biological changes by stimulating fibroblasts, leading to the production and reorganization of collagen and elastin fibers [27]. This could, for example, improve the healing of an episiotomy and secondarily enhance the muscular qualities of the PFM. In women with chronic pelvic pain and dyspareunia, radiofrequency appears to reduce pain, improve sexual function, enhance PFM strength, and alleviate urinary incontinence symptoms. However, the quality of the evidence, the heterogeneity of the treatment protocols, and the small sample sizes highlight the need for further studies to confirm its effectiveness [28]. Only one randomized clinical trial (RCT) conducted in postpartum women has analyzed the efficacy of radiofrequency on pelvic pain 3 to 6 months after delivery. This study compared five sessions of radiofrequency with five sessions of manual therapy targeting the PFM. Both groups reported improvements in subjective perceptions of pain relief and overall improvement; however, only the radiofrequency group demonstrated increased vaginal laxity [29]. Nevertheless, no significant improvements in PFM neuromuscular activity were observed, likely due to the absence of a multimodal physiotherapy approach that included PFMT and educational strategies. Additionally, the study did not evaluate sexual function and focused solely on short-term effects, despite this population being at risk of developing new pelvic floor symptoms, including pelvic pain, when resuming to work, sports, or sexual activity. Therefore, it is essential to incorporate preventive therapeutic strategies and home self-management techniques during the postpartum period [30].

The long-term maintenance of positive outcomes depends not only on the treatment but also on behavioral changes and adherence to the physiotherapist’s recommendations [31]. Therefore, exploring and understanding women’s motivation, perceived self-efficacy, and expectations, among other factors, seems essential to ensuring the long-term effectiveness of conservative treatments [32].

The RASDOP study is designed to (i) compare standard multimodal physiotherapy for postpartum pelvic pain with an experimental approach that includes radiofrequency therapy, whose efficacy and safety remain unknown; and (ii) explore factors influencing therapeutic adherence and perceived self-efficacy, identifying the challenges and facilitators that affect postpartum women in adopting and maintaining recommended practices for long-term benefits.

Our hypothesis is that the inclusion of radiofrequency within a multimodal physiotherapy treatment enhances its efficacy in managing postpartum pelvic pain by reducing pain, improving sexual function, eliminating the presence of MPS in the PFM, and improving PFM qualities. Additionally, factors influencing postpartum women’s adherence or non-adherence to a conservative treatment plan for pelvic pain will be explored. These findings will assist clinicians in decision-making regarding the inclusion of technologies such as radiofrequency in the management of pain in this population and provide insights to guide the development of a biopsychosocial approach to postpartum pain treatment.

## 2. Materials and Methods

### 2.1. Study Design

The RASDOP study is a mixed-methods study comprising a single-blind RCT and a qualitative component. The RCT will follow a two-parallel-arm design. Outcome assessment will be blinded, meaning that the evaluators conducting the assessments will not be aware of the participants’ group allocation to reduce detection bias. However, due to the nature of the interventions, neither participants nor treating physiotherapists will be blinded. In parallel, a qualitative study will be conducted using a phenomenological approach, involving individual and group interviews with women from the RCT.

This study has been approved by the Research and Animal Experimentation Ethics Committee of the University of Alcalá under registration number CEIP/2023/3/056. This study has also been registered on the ClinicalTrials.gov platform under the identification code NCT06469632.

### 2.2. Randomized Controlled Clinical Trial

All procedures will be conducted in compliance with the ethical principles of the Declaration of Helsinki and guided by the CONSORT recommendations for clinical trials [33]. The presentation of this protocol follows the guidelines of the SPIRIT 2013 Statement for protocol publication [34].

#### 2.2.1. Study Participants

Postpartum women experiencing pelvic pain following a vaginal delivery, referred by the Gynecology and Obstetrics Department of Príncipe de Asturias University Hospital for physiotherapy assessment. Physiotherapy assessments and treatments will be conducted at the laboratory of the Physiotherapy in Women’s Health (FPSM) Research Group at the University of Alcalá.

The inclusion criteria will be primiparous women who have had a vaginal delivery, within the past 6 weeks–6 months, experiencing postpartum pelvic pain with an intensity of ≥4 cm on the visual analog scale, and who have read, understood, and freely signed the informed consent. Women will be excluded if they are multiparous, have undergone instrumental vaginal delivery or cesarean section, experienced avulsion of the levator ani muscle, sustained a third- or fourth-degree perineal tear, have a history of pelvic fractures and/or neoplasms, are pregnant, have neurological conditions, an active vaginal or urinary tract infection, an intrauterine device with metallic components, or cognitive, auditory, and/or visual impairments that prevent them from understanding the information, responding to questionnaires, providing consent, and/or participating in the study. Women who have received or are currently undergoing medical or physiotherapeutic treatment for pelvic pain will also be excluded. The enrollment, allocation, treatment, and follow-up scheme for the participants is shown in Figure 1.

#### 2.2.2. Sample Size

The sample size was calculated based on the results obtained by Citak et al. [35], using the Female Sexual Function Index (FSFI) scores as a reference and the statistical program GRANMO 8.0 (Datarus, Barcelona, Spain). Assuming a two-tailed test with an alpha risk of 0.05 and a statistical power greater than 0.8, 62 participants per group will be required to detect a difference of 2.4 points or greater. A common standard deviation of 4.5 was assumed. Additionally, a 10% dropout rate was accounted for in the estimation.

#### 2.2.3. Physiotherapy Assessments

Physiotherapy assessments will be conducted by a physiotherapist specializing in Pelvic and Women’s Health (PT1) with over 10 years of experience, who will be blinded to the participants’ intervention group. The physiotherapy assessment will include an interview to collect socio-demographic and clinical history data, as well as a physical examination (Table 1). The outcome variables of the study that will be collected at all assessments are as follows:Primary outcomes:
(1)Pelvic pain: The perceived pain intensity will be measured using the Visual Analog Scale (VAS). This scale consists of a 100 mm horizontal line, where the participant marks the intensity of their pain, with the left margin of the line representing “no pain” and the right margin representing “the worst possible pain.” A minimum detectable change (MDC) of 15 mm is required for clinical significance [36].(2)Female sexual function: The Spanish version of the FSFI will be used [37]. The FSFI questionnaire has a scoring range from 2 to 36 points, with higher scores indicating better sexual function. It assesses six domains: desire, arousal, lubrication, orgasm, satisfaction, and pain. A change of 6 points will be considered clinically relevant [38].Secondary outcomes:
(1)Myofascial pain syndrome (MPS): The presence of MPS will be identified by assessing myofascial trigger points (MTrPs) in the abdominal muscles and PFM. To diagnose MPS, at least one active MTrP must be identified. The essential clinical criteria proposed by Travell and Simons will be followed (Table 2) [39]. Additionally, confirmatory observations will be recorded, such as the presence of referred pain elicited by palpating the MTrP [40].(2)Pelvic floor dysfunction perceived distress: Evaluated using the transculturally validated Spanish version of the Pelvic Floor Distress Inventory–short form (PFDI-20) [41]. The PFDI-20 is scored from 0 to 300, with higher scores indicating greater distress caused by pelvic floor dysfunctions. It assesses lower urinary tract symptoms, anorectal symptoms, and pelvic organ prolapse symptoms. A minimal important change of 23% will be considered clinically significant [42].(3)Impact of pelvic floor dysfunctions: Assessed using the Spanish version of the Pelvic Floor Impact Questionnaire–short form (PFIQ-7) [41], which includes three subscales related to urinary, intestinal, and prolapse symptoms. Each subscale is scored from 0 to 100, where a higher score indicates a greater impact and worse quality of life. An MDC of 16% is required for clinical significance [43].(4)Pelvic floor muscles tone: PFM tone will be assessed using vaginal dynamometry (Pelvimetre™, Phenix Vivaltis, Montpellier, France). The participant will be in the lithotomy position, and the lowest value automatically recorded by the device will be taken after instructing the woman to relax her PFM. A MDC of 5 g will be considered [44].(5)Pelvic floor muscle strength: PFM strength will be measured in the lithotomy position by requesting three maximal PFM contractions. The average value of the three contractions will be considered. A vaginal dynamometer (Pelvimetre™, Phenix Vivaltis, Montpellier, France) will be used for the measurement, and a MDC of 50 g will be considered [44].(6)Levator hiatus length: Using 2D transperineal ultrasound (Mindray M7, Shenzhen, China) in the sagittal plane, the distance between the inferior margin of the pubic symphysis and the anorectal angle will be assessed [45]. Measurements will be taken at rest, during maximal PFM contraction, and during a strain effort.(7)Perceived self-efficacy: assessed using the Broome Pelvic Muscle Self-Efficacy Scale–Spanish version [46]. This scale evaluates expectations of self-efficacy in performing specific PFM exercises and expectations regarding the anticipated outcomes. The maximum score is 100 points, indicating high self-efficacy, while a score below 33 points indicates low self-efficacy [46].

**Table 1 jcm-14-01489-t001:** Study assessed variables and evaluations.

Assessed Variables	Assessment				
	A0	A1	A2	A3	A4
Sociodemographic variables (address, telephone number, mail, profession, studies, date of birth)	X	only if changes	only if changes	only if changes	only if changes
General clinical data (weight, height, medication, diagnosed pathologies, surgeries, allergies, sports routines, healthy habits)	X	only if changes	only if changes	only if changes	only if changes
Gynecological history (pregnancies, weight gain during pregnancy, type of delivery, presence and degree of tear, presence of episiotomy, weight and length of the baby, breastfeeding, menstruation, symptoms of pelvic floor dysfunction)	X	only if changes	only if changes	only if changes	only if changes
Pelvic floor observation (contraction capacity, relaxation capacity, apnea, parasitic muscle contraction, reflexes, symmetries, perineal scars)	X	X	X	X	X
PFM objective evaluation (Modified Oxford scale, tone and strength by vaginal dynamometry; rest, PFM contraction and bearing down by transperineal ultrasound)	X	X	X	X	X
Diagnosis of MPS (pain: description, intensity, body chart, triggering factor; palpation of abdominal and pelvic floor surface and deep muscles)	X	X	X	X	X
Questionnaires (FSFI, PFDI-20, PFIQ-7, Broome scale)	X	X	X	X	X

A0: pre-treatment assessment, A1: post-treatment assessment, A2: 3-month assessment after treatment, A3: 6-month assessment after treatment, A4: 12-month assessment after treatment, PFM: pelvic floor muscles, MPS: myofascial pain syndrome, FSFI: Female Sexual Function Index, PFDI-20: Pelvic Floor Distress Inventory–short form, PFIQ-7: Pelvic Floor Impact Questionnaire–short form.

**Table 2 jcm-14-01489-t002:** Diagnostic clinical criteria for identifying active and latent myofascial trigger points.

Essential Criteria	Active MTrPs	Latent MTrPs
Palpable taut band	X	X
Exquisite local tenderness upon pressure over a nodule within the taut band	X	X
Patient recognition of their typical pain upon pressure applied to the tender nodule	X	
Painful limitation of the range of motion upon full muscle stretch	X	X

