### 3.1. RASDOP Randomized Controlled Clinical Trial Expected Results

The multimodal physiotherapy intervention, based on therapeutic education, PFMT, treatment of MPS in the abdominal and/or PFM, and the use of radiofrequency in women with pelvic pain after childbirth, is expected to significantly improve pelvic floor symptoms in these women. Thus, the RASDOP study is proposed as a solution to improve symptoms related to pelvic pain, the potential occurrence of urinary incontinence, increased urinary frequency, or even the presence of involuntary gas leakage in the postpartum period.

A significant improvement is expected in sexual function, particularly in the domains of lubrication, orgasm, and pain, as assessed by the FSFI questionnaire. Regarding distress and the impact of other pelvic floor dysfunctions, such as lower urinary tract issues, pelvic organ prolapse, and anorectal dysfunctions, evaluated through the PFDI-20 and PFIQ-7 questionnaires, a decrease of more than a 23% in the scores is anticipated, indicating an improvement in symptoms and a reduced impact on quality of life [48].

An increase in the strength of the PFM is expected, as measured by vaginal dynamometry, due to the performance of PFMT and the adoption of healthy PFM protection habits. In contrast, an improvement in the relaxation capacity and elasticity of the PFM is anticipated, as assessed by transperineal ultrasound.

It is expected that the presence of MTrPs in the abdominal muscles and PFM will decrease or even be eliminated. In cases where MTrPs are still palpated, it is anticipated that they will be latent and not trigger painful symptoms in the women.

The Broome scale will be used to assess self-confidence and self-efficacy in performing PFMT, as well as changes in lifestyle behavior, which are expected to help sustain treatment benefits in the long term. It is anticipated that participants in both groups will achieve a score of over 66 points on the Broome scale during the post-treatment and follow-up evaluations, indicating a high perception of self-efficacy [46].

Although both intervention groups are expected to show significant improvements between the pre- and post-treatment assessments, and maintain their results at 3-, 6- and 12-month stages post-treatment, it is anticipated that these improvements will be greater in all variables in the RMP-G group, particularly in sexual function, pain reduction, and the lower presence of MTrPs.

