## 4. Discussion

To the authors’ knowledge, this is the first RCT with evaluator blinding to compare the effectiveness of a multimodal physiotherapy treatment versus a multimodal treatment that includes non-ablative radiofrequency in managing pelvic pain and sexual function from six weeks to six months postpartum. The significance of the RASDOP study lies in addressing the fact that nearly 50% of women develop symptoms of pelvic pain and/or dyspareunia following childbirth [12,13]. If left untreated, this pain can persist over time [49], negatively impacting sexual function, mental health [50], quality of life, and even the desire to have more children.

Previous studies have evaluated the efficacy of radiofrequency in pelvic pain immediately after childbirth [51,52]. These include two double-blind RCTs comparing the immediate use of radiofrequency versus placebo in women following vaginal delivery. Two consecutive sessions were conducted during the participants’ hospital stay, and perineal pain was assessed at rest, while sitting, and during walking. Bretelle et al. [51] reported improvements in walking pain and reduced analgesic consumption in the study group. In contrast, Sierenska et al. [52] found that radiofrequency improved pain and discomfort at rest, while sitting, and while walking but did not observe a reduction in the consumption of paracetamol or ibuprofen. In the acute phase, perineal trauma can be the primary source of pain, which may sometimes improve with medication or local cooling [53]. However, this pain can persist over time, potentially involving other structures, such as the PFM, as the primary source of discomfort. The RASDOP study proposes applying radiofrequency not only to scars but also to the PFM and abdominal muscles, aiming to improve the MTrPs in these muscles. Radiofrequency has only demonstrated short-term effects, and existing studies have heterogeneous protocols, small sample sizes, or lack a control group [28]. Therefore, more evidence is needed to support the use of radiofrequency for pelvic pain, as well as the additional financial cost associated with this technology. Additionally, radiofrequency is a passive treatment technique, while maintaining long-term benefits requires behavioral modifications and the adoption of active treatment strategies [54]. Therefore, the RASDOP study will include educational management and PFMT in both treatment groups.

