The classification of pelvic pain is controversial and varies depending on the source consulted. This study will include women with pelvic pain without infection or obvious local pathology, which, according to the International Association for the Study of Pain (IASP) classification, is considered primary pelvic pain syndrome [1]. Since the study will assess the presence of MPS in PFM and abdominal muscles, we will follow the classification provided by the European Association of Urology [2], based on IASP recommendations. Therefore, primary pelvic floor muscle pain syndrome and coccyx pain syndrome, both associated with musculoskeletal pain, will be included.

Among the strengths of the RASDOP study is its design as an RCT conducted by experienced physiotherapists specializing in clinical practice and research in Pelvic and Women’s Health. Participants will be referred by a gynecology service that has maintained a referral relationship for over 15 years, ensuring high-quality conservative treatment for women—a service currently not provided free of charge in Spain. The study’s rigorous design will allow for the evaluation of the efficacy and safety of incorporating radiofrequency technology, an increasingly utilized intervention in clinical settings but with limited supporting evidence to date. Another notable strength is the comprehensive outcome measures to be collected. These will include subjective aspects and quality-of-life impacts, as well as objective local physical changes in the pelvic floor. This will be the first study to assess changes in sexual function and other pelvic floor dysfunctions, such as urinary and/or anal incontinence and pelvic organ prolapse, as well as changes in PFM tone, strength, and morphology in postpartum women experiencing pain who undergo physiotherapy treatment that incorporates radiofrequency. Additionally, the follow-up period will span one year, whereas published studies in this field have only reported immediate post-intervention results [29,51,52].

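### The hypothesis concerns myofascial pain syndrome in the pelvic floor muscles, but the outcome pools abdominal and pelvic floor trigger points and defines no pelvic floor result

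*Protocol article*

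**What the plan says.** - **Hypothesis (section 1, Introduction).** Adding radiofrequency is expected to improve efficacy by, among other things, "eliminating the presence of MPS in the PFM, and improving PFM qualities". Only the PFM are named.
- **Outcome (section 2.2.3, secondary outcome 1).** "The presence of MPS will be identified by assessing myofascial trigger points (MTrPs) in the abdominal muscles and PFM". The threshold follows: "To diagnose MPS, at least one active MTrP must be identified". No PFM-specific version is defined.
- **Expected results (section 3.1).** These cover both sites: "It is expected that the presence of MTrPs in the abdominal muscles and PFM will decrease or even be eliminated". A lower presence of trigger points is one of three areas in which the radiofrequency group is particularly expected to do better.
- **Where radiofrequency is applied.** The Discussion says "not only to scars but also to the PFM and abdominal muscles, aiming to improve the MTrPs in these muscles". Section 2.2.5 describes application to the scar, perineal body and labia majora, inside the vagina and, on the abdominal side, over the suprapubic region only.
- **Entry (section 2.2.1).** Women must be "experiencing postpartum pelvic pain with an intensity of ≥4 cm on the visual analog scale". No trigger point is required.
- **Analysis (section 2.2.6).** Dichotomous outcomes are compared by Chi-square or Fisher's exact test, and the main group comparison is to be adjusted for the baseline value of the outcome.
- **Data collected (Table 1).** Abdominal and pelvic floor muscles are both palpated at A0 to A4.

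**The concern.** An outcome that is positive when either of two sites is positive does not measure what happens at one of them. Two errors are possible, in opposite directions.

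- If radiofrequency clears PFM points but leaves abdominal points alone, the women who keep an abdominal point stay positive, and a real PFM effect shrinks or disappears.
- If radiofrequency mainly changes abdominal points, the pooled outcome improves and can be reported as support for a hypothesis about the pelvic floor.

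In either case the defined outcome does not answer the question in the Introduction. Separately, a woman with no active PFM point at A0 cannot show elimination of PFM MPS, so the hypothesised event is possible only in a subset whose size the article does not state.

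**Working it through.** **The plan's own figure.** The article gives no number for MPS. Its sample size rests on the Female Sexual Function Index (FSFI): difference 2.4, SD 4.5, two-sided alpha 0.05, power 0.80.

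n = 2 × (1.96 + 0.84)² × 4.5² / 2.4² ≈ 55.2, so 56 per arm. For 10% dropout, 56 × 1.10 = 61.6, which rounds up to the stated 62 (56 / 0.90 = 62.2, or 63, by the other convention). The figure reproduces and does not depend on this point. I use 56 completers per arm below.

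**Assumed inputs (none is given for this trial).**
- Share of women with PFM MPS at A0: b = 0.85. The Discussion's upper figure for women with pelvic floor dysfunctions is used as a starting value; 0.70 and 0.50 are also shown.
- PFM MPS persists in 0.50 (control) and 0.25 (radiofrequency) of these women.
- Abdominal points persist, independently, in a = 0.30 of these women in the control arm. In the radiofrequency arm a is either 0.30 (no abdominal effect) or 0.15 (halved).
- No new cases among women negative at A0.

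**Formulas.**
- Pooled outcome, all women: P = b × [1 − (1 − PFM persistence) × (1 − a)]
- PFM only, all women: P = b × PFM persistence
- Power = Φ[(|p1 − p2| − 1.96 × √(2p̄(1 − p̄)/n)) / √((p1(1 − p1) + p2(1 − p2))/n)], where p̄ is the mean of p1 and p2

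**Results at b = 0.85.**
- *Pooled, no abdominal effect.* Control 0.85 × (1 − 0.50 × 0.70) = 0.5525; radiofrequency 0.85 × (1 − 0.75 × 0.70) = 0.4038. Difference 14.9 points, n = 56, power 0.35.
- *Pooled, abdominal persistence halved.* Radiofrequency 0.85 × (1 − 0.75 × 0.85) = 0.3081. Difference 24.4 points, n = 56, power 0.75.
- *PFM only, all women.* 0.425 vs 0.2125. Difference 21.2 points, n = 56, power 0.68.
- *PFM only, women positive at A0.* 0.50 vs 0.25. Difference 25 points, n = 0.85 × 56 ≈ 48, power 0.72.

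**Power by share with PFM MPS at A0.**

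| Share at A0 | Pooled, no abdominal effect | Pooled, abdominal halved | PFM only, all women | PFM only, A0-positive |
|---|---|---|---|---|
| 0.85 | 0.35 | 0.75 | 0.68 | 0.72 (n = 48) |
| 0.70 | 0.26 | 0.61 | 0.56 | 0.63 (n = 39) |
| 0.50 | 0.18 | 0.42 | 0.39 | 0.49 (n = 28) |

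If the abdominal rate applies to all women instead of only those with PFM MPS at A0, the pooled figures at b = 0.85 become 1 − 0.575 × 0.70 = 0.5975 vs 1 − 0.7875 × 0.70 = 0.4488 (power 0.35), or vs 1 − 0.7875 × 0.85 = 0.3306 (power 0.82).

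**Reading.** At b = 0.85, moving from A0-positive women to all women costs little (0.72 to 0.68). What moves the result is the unknown abdominal effect, which takes the pooled outcome anywhere from well below the PFM-only comparison to slightly above it.

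**The case against.** The strongest reply is that the two-site outcome is what the trial intends. Section 3.1 states the expected result for both sites, the Discussion names the abdominal muscles as a target of radiofrequency, and the Conclusions speak of managing MPS in both. On that view the Introduction is merely the narrower sentence. This stands against any claim that the effect is diluted. A reader might infer certain dilution from the mismatch, but that needs radiofrequency to do nothing to abdominal points. The documents do not say so, and with abdominal persistence halved the pooled outcome loses no power. It does not remove the mismatch: even then, a pooled result cannot show that PFM MPS was eliminated.

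A second reply concerns women without MPS at entry. Comparing presence in all randomised women is a legitimate estimand that also captures new or recurrent points, and section 2.2.6 promises baseline adjustment. If women negative at A0 have no events, an analysis stratified on A0 status draws nothing from them, so most of the loss goes. This largely stands. The Chi-square and Fisher tests named for dichotomous outcomes do not themselves adjust, but the choice of model can sit in an analysis plan. Adjustment still cannot turn an any-site outcome into a PFM outcome.

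A reader might also see a contradiction between the entry criteria and the Discussion's statement that "primary pelvic floor muscle pain syndrome and coccyx pain syndrome, both associated with musculoskeletal pain, will be included". There is none: that sentence classifies the pain syndromes admitted and does not say that every woman has a PFM trigger point.

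Finally, site-level tables may be planned elsewhere. That is possible, but the article does state the rule for diagnosing MPS, and that stated rule does not match the stated hypothesis.

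**Conclusion.** The mismatch is real. The hypothesis is about PFM MPS; the outcome as defined is any active point in abdominal or pelvic floor muscles, with no PFM-specific result. It can mislead in either direction.

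Its size cannot be fixed from the documents. With 85% positive at A0, PFM persistence of 50% vs 25% and control-arm abdominal persistence of 30%, power for the pooled outcome is about 0.35 with no abdominal effect and about 0.75 with abdominal persistence halved, against about 0.72 for PFM-only in A0-positive women. Every one of these rates is an assumption; the 85% comes from another population. The figures show how much rests on the abdominal effect. They do not show that the planned comparison is underpowered.

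This is a secondary outcome with no power claim. The primary outcomes and the FSFI-based sample size are untouched.

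**What to change.** 1. In section 2.2.3, score active trigger points separately for the PFM and the abdominal muscles, using the palpation already listed in Table 1 for A0 to A4.
2. Make presence of any active PFM trigger point the result that tests the Introduction's hypothesis, compared between groups with adjustment for PFM MPS at A0, in line with section 2.2.6.
3. Report elimination among women with at least one active PFM trigger point at A0. This subset is fixed before treatment. Whether to make it the main MPS analysis is a choice of estimand and is not required.
4. Keep abdominal MPS and any-site MPS as supporting results.
5. Reconcile section 2.2.5 and the Discussion on which abdominal areas receive radiofrequency, so that readers can interpret the abdominal result.

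The cost is a reworded outcome definition and one or two more secondary tabulations. No visit, measurement or sample size changes.
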